## Abstract

**Background:**

Type 2 diabetes mellitus (T2DM) is a growing global health concern. In 2016, 9.7% of Bruneian adults aged 18 to 69 years had diabetes, making it the third leading cause of death. Effective self-management can mitigate complications that require health care interventions and lower health care costs. Brunei Darussalam has deployed BruHealth, a national mobile health platform synced with the Brunei Health Information Management System, allowing patients to access health records, schedule appointments, and explore medical articles. A digital therapeutics module for T2DM (diabetes mellitus digital therapeutics [DM DTx]) has been developed, consisting of a digital lifestyle intervention module within BruHealth and a separate health care professional portal for health coaches. The 16-week BALANCE program aims to support self-management. This study explores the efficacy of DM DTx in managing T2DM through digital lifestyle interventions.

**Objective:**

The primary objective is to determine the proportion of participants who achieve at least a 0.6% reduction in glycated hemoglobin after 16 weeks. Secondary objectives include evaluating changes in glycated hemoglobin, fasting lipid profile, blood glucose, BMI, and waist circumference and analyzing participant feedback. Given the predominantly Muslim population, the study also aims to gain insight into fasting practices for Muslim participants with T2DM.

**Methods:**

This single-arm, nonrandomized intervention study involves adults aged 18 to 70 years with T2DM. Participants complete a fully online 16-week program via BruHealth that includes diabetes self-management education, personalized diet and exercise plans, self-monitoring tools (eg, glucometer and smartwatch), and support from health coaches through video consultations and instant messaging. Anthropometric and biochemical measures are collected at baseline and after the intervention. Data sources include the Brunei Health Information Management System, BruHealth app logs, and the health care professional portal. Descriptive statistics will summarize participant characteristics and outcomes. Paired 2-tailed *t* tests or Wilcoxon signed-rank tests will compare the results before and after the intervention. Subgroup analyses will explore outcomes based on glycemic changes, BMI, medication type, and program engagement. Participant feedback will be qualitatively analyzed. Fasting risk in Muslim participants will be stratified using the International Diabetes Federation-Diabetes and Ramadan Alliance Risk score.

**Results:**

Recruitment began on August 20, 2024, following project approval in July 2024, and continued until July 2025. By the end of data collection on November 12, 2025, a total of 459 participants had been enrolled, and 422 (91.9%) had completed the program. Data analysis is currently ongoing, with results expected in early 2026.

**Conclusions:**

Self-management mobile health apps are promising tools for chronic disease management, including T2DM. The BALANCE program is Brunei’s first national-scale study evaluating a fully online T2DM intervention. Localization to a region’s population may support improved health outcomes.

**International Registered Report Identifier (IRRID):**

DERR1-10.2196/73964

## Introduction

### Background

Type 2 diabetes mellitus (T2DM) has emerged as a significant global health concern, with a worldwide prevalence of 537 million adults in 2021, and it is projected to rise to 783 million by 2045 [1]. In 2016, 9.7% of Bruneians aged between 18 and 69 years were diagnosed with diabetes [2]. Diabetes is the third leading cause of death in Brunei Darussalam, accounting for 10.1% of total deaths in 2017 [3]. Therefore, there is a need for effective management strategies tailored for patients with T2DM to achieve target glycemic control and reduce the risks of developing complications. This will lead to more efficient use of health resources.

In Brunei Darussalam, diabetes-related health care costs strain the national budget and heighten demand for services necessary to manage complications related to diabetes. The global cost of diabetes was estimated at US $966 billion in 2021 and is projected to rise to US $1.03 trillion by 2045 [1]. This burden includes direct medical expenses and indirect costs from increased prescription use, costly hospital services, and complications that can reduce overall productivity and lead to unemployment [4,5].

T2DM is a chronic disease that can lead to severe complications if not managed appropriately [6]. This underscores the critical role of self-management. Effective lifestyle management, which incorporates regular physical activity, a healthy diet, and medication adherence, can reduce both disease complication risks and health care costs [7]. By using SMART (specific, measurable, achievable, relevant, and time-bound) goals and behavioral techniques, individuals can improve their diabetes control and disease outcomes [8]. Recent studies have demonstrated that digital health interventions favorably impact glycemic control, patient adherence, and engagement [9,10]. Additionally, mobile health (mHealth) apps have been shown to positively improve health self-management practices on chronic conditions [11-13].

The digitalization of health care can further benefit the management of chronic diseases, such as T2DM [14]. With mobile ownership reaching 78% globally [15], health care can access a broad audience, enhancing health equity by providing vital information and resources. This accessibility equips underserved populations with tools for effective self-management, such as tracking health metrics and connecting with health care providers for personalized guidance.

BruHealth is the national mHealth app and health care portal in Brunei Darussalam, initially developed to mitigate COVID-19 spread. It has since evolved into a comprehensive digital health solution, benefiting the general population. The app is synchronized with the Brunei Darussalam Health Care Information and Management System (BruHIMS), where 95% of the population has active health records, allowing real-time access to health care data. Users can view their health records through BruHealth, enabling them to monitor their health status and access their blood test results. Beyond pandemic-related features, BruHealth now offers online appointment scheduling, health assessments, and access to medical articles on topics such as nutrition and lifestyle. By providing an accessible, user-friendly platform, BruHealth promotes the adoption of digital health technologies while allowing users to manage their health effectively [16].

Most existing global digital therapeutics (DTx) apps function as stand-alone tools, often relying on self-reported data and offering limited integration with national health systems. These apps frequently incur additional costs to users and typically focus on a single behavioral domain, such as diet tracking or medication adherence, thereby limiting their impact. The BALANCE program, delivered through BruHealth, adopts a holistic and culturally contextualized approach to diabetes prevention and management. The program addresses multiple lifestyle domains and provides education that has been adapted to the lifestyle in Brunei. Through integration with reliable wearables and BruHIMS, data captured can be used to create an appropriate health plan, enabling users to monitor their condition more seamlessly. This centralized and personalized system overcomes the key limitations of conventional DTx tools, particularly by offering a tailored and accessible solution for Brunei’s population [17]. The digitalization of this tool also increases accessibility to services and education that would otherwise be available only in person.

### Rationale

DTx are software-based treatments that deliver interventions with the best available evidence to manage or prevent diseases. They supplement or replace traditional therapies and are prescribed for chronic conditions such as diabetes and mental health disorders. In Brunei Darussalam, a DTx module focused on the management of T2DM (diabetes mellitus DTx [DM DTx]) has been developed.

The benefits of the DM DTx include patient education on diabetes management through lifestyle adjustments for better glycemic control, and real-time advice that has been designed to seamlessly integrate into daily activities, thus enabling patients to self-manage their diabetes with greater confidence. DM DTx may improve self-management and the quality of life of individuals with T2DM while paving the way for a more efficient and effective health care model.

The DM DTx module consists of a digital lifestyle intervention (named the BALANCE program, which is integrated into the BruHealth app) and a health care professional (HCP) portal where health coaches can interact with their patients and help them manage their condition. The BALANCE program has evolved from a previous pilot study conducted to evaluate the efficacy and feasibility of a digital lifestyle intervention for T2DM [18]. The pilot intervention program was designed with the expertise of endocrinologists and dietitians based on national clinical guidelines and evidence-based practice in diabetes management. Following further refinement and complete digitalization of the initial program, our study aims to assess the potential impact of a T2DM digital intervention that uses a fully online management approach.

Separately, as Brunei Darussalam has a Muslim-majority community, there is an optional component within the DM DTx offered to Muslim participants as an opportunistic way of gaining more insights into their fasting practices during the last Ramadan. Studies have shown that a significant number of Muslim patients in Brunei Darussalam with diabetes fast during Ramadan. For instance, a study found that 93.4% of participants fasted during Ramadan, with an average of 24.1 days. This optional component in the DM DTx could provide valuable insights into how fasting impacts diabetes management and help tailor more effective treatment plans for Muslim patients [19].

### Aims and Objectives

Our study aims to evaluate the efficacy of the DM DTx in managing patients with T2DM by delivering digital lifestyle interventions through an easily accessible platform (BruHealth), and to evaluate participants’ feedback to improve the app’s content and structure for better user experience.

The primary objective is to determine the proportion of participants who achieve at least a 0.6% reduction in glycated hemoglobin (HbA_1c_) from baseline following a 16-week lifestyle intervention provided by the DM DTx module. Secondary objectives are (1) to evaluate overall changes in HbA_1c_, fasting lipid profile, fasting blood glucose, BMI, and waist circumference over a 16-week period; (2) to analyze participants’ feedback on the BALANCE program; and (3) to evaluate fasting experience among Muslims with T2DM during Ramadan and to calculate their fasting risk using the International Diabetes Federation-Diabetes and Ramadan Alliance Risk (IDF-DAR) score [20].

## Methods

### Study Design

This is a single-arm, nonrandomized intervention study that involves the use of BALANCE, a 16-week diabetes lifestyle management program (described in more detail subsequently under the “Intervention” section). Patients with T2DM are enrolled and taught diabetes self-management with structured educational courses, and their progress is monitored through the DM DTx with dedicated health coaches.

Anthropometric measurements are taken at baseline and at the end of the study. These include BMI (height and weight) and waist circumference. A fasting blood sample is also taken at baseline and at the end of the study. The blood tests include the following:

Fasting blood glucoseHbA_1c_Fasting lipid profile (total cholesterol, triglycerides, low-density lipoprotein cholesterol, and high-density lipoprotein cholesterol)

Serum creatinine is also measured at baseline if there is no result available within 1 year of enrollment.

### Participants

#### Sample Size

By using a paired 2-tailed *t* test, a sample of 439 participants will provide 90% power to detect a 0.14 effect size at a .05 significance level. Considering a potential attrition rate of 12% based on the previous pilot study, the target sample size has been set at 500 participants.

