## Results

Recruitment began on August 20, 2024, following project approval in July 2024, and continued until July 2025. By the end of data collection on November 12, 2025, a total of 459 participants had been enrolled, and 422 (91.9%) had completed the program. Data analysis is currently ongoing, with results expected in early 2026 (Figure 11).

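### The 439 participants give about 83% power, not 90%, for the stated two-tailed test; 439 is exactly the one-tailed sample size

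*Protocol article*

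**What the plan says.** The Sample Size paragraph of the protocol article gives every input to the calculation. The test is set out by "By using a paired 2-tailed *t* test", and the claim is that "a sample of 439 participants will provide 90% power to detect a 0.14 effect size at a .05 significance level". It then allows for 12% attrition, taken from the pilot study, and sets the target at 500.

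The Methods paragraph of the abstract also describes the planned paired t tests as two-tailed, in the sentence that continues "tests or Wilcoxon signed-rank tests will compare the results before and after the intervention". The article nowhere mentions a one-tailed test.

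The Results section reports that "a total of 459 participants had been enrolled, and 422 (91.9%) had completed the program".

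**The concern.** Test, sidedness, alpha, effect size, sample size and power all stand in one sentence, so any one of them can be checked against the rest. For a two-tailed test at .05, 439 pairs looked too few to give 90% power at an effect as small as 0.14.

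This is the article's only justification of the sample size. If it is wrong, the study never had the power it claims for the paired comparisons, and the enrolment target inherits the error. Non-significant changes in HbA1c, glucose, lipids, BMI or waist circumference would then be read against a 10% type II error that the design did not deliver.

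**Working it through.** **Inputs, all from the Sample Size paragraph.** Paired t test, two-tailed; alpha .05; standardised effect d = 0.14; n = 439; power 90%; attrition 12%; target 500. From Results: 459 enrolled, 422 completed. I read d as the mean paired change divided by the SD of the paired changes, which is the usual meaning for a paired t test; the article does not define it.

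**Formula.** The test statistic follows a non-central t distribution with df = n − 1 and non-centrality d√n. Power is the probability of falling beyond the critical value: the upper .05 point if one-tailed, the upper and lower .025 points if two-tailed. The normal approximation to the sample size is n = ((z_alpha + z_power)/d)².

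**Reproducing 439.**

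- Two-tailed, approximate: ((1.960 + 1.282)/0.14)² ≈ 536.1, so 537.
- Two-tailed, exact: the smallest n with at least 90% power is 539.
- One-tailed, approximate: ((1.645 + 1.282)/0.14)² ≈ 436.9, so 437.
- One-tailed, exact: the smallest n is 439 (power 0.9004; 438 gives 0.8998).

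The plan's figure is recovered to the integer by the one-tailed test and missed by 100 pairs (100/439 = 23%) by the two-tailed test.

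**Power at d = 0.14, exact.**

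| n | Two-tailed | One-tailed |
|---|---|---|
| 422 (completers) | 81.8% | 89.0% |
| 439 (stated) | 83.3% | 90.0% |
| 440 (500 less 12%) | 83.4% | 90.1% |
| 500 (no attrition) | 87.8% | 93.1% |

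As a hand check at 439: 0.14 × √439 = 2.933, and Φ(2.933 − 1.960) = Φ(0.973) ≈ 0.835, close to the exact 0.833.

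**Effect detectable with 90% two-tailed power.** 0.155 at n = 439 and 0.158 at n = 422.

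**Attrition step.** 439/0.88 = 498.9, so 499, rounded up to 500. This step is consistent and shows that 439 fed the target. The two-tailed requirement would have been 539/0.88 = 612.5, so 613 enrolled.

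**Can another reading rescue the statement?**

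- If 0.14 is rounded, d lies between 0.135 and 0.145, and the two-tailed n runs from 579 down to 502.
- If 0.1499 had been truncated to 0.14, the two-tailed n is still 470.
- The Wilcoxon alternative needs more pairs for normally distributed changes: 539/(3/π) = 564.4, so 565.
- Two-tailed power of 80% would need 403 and 85% would need 461, so 439 is not the answer for those round power values either.

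**The case against.** The arithmetic is not in dispute. The objections concern weight and scope.

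- **Nothing operational changes.** Recruitment and data collection are over, power stays above 80%, and the effect detectable with 90% power moves only from 0.14 to 0.155. Inference will rest on observed estimates and their precision, and the article already concedes that a single-arm design cannot attribute effects to the intervention. This is true and is why no extra enrolment is asked for. It does not make the printed figure right.
- **The primary outcome is a proportion.** It is the share of participants whose HbA1c falls by at least 0.6%. The power of a t test on a mean change does not describe that outcome, and the article does not name the variable to which 0.14 refers. This stands: the correction concerns the power claim for paired mean changes and says nothing about precision for the primary proportion.
- **The one-tailed origin is inferred.** The article does not state it. The match to the integer makes it very likely, but the error does not depend on it: whatever its source, 439 does not give 90% two-tailed power.
- **Under-recruitment is not a planning error.** Agreed. Enrolment of 459 missed the target of 500 (though it exceeded 439), and the 422 completers fall short of 439. The article reports these numbers openly. They widen the gap but did not create it, and power at the achieved number should be labelled separately from the planning statement.

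**Conclusion.** The sample-size statement is wrong as written. With its own inputs, two-tailed power is 83.3% rather than 90%, and 90% power would have needed 539 evaluable pairs rather than 439. The type II error at the planning effect is 16.7%, about 1.7 times the stated 10%. With 422 pairs, power is 81.8% and the type II error 18.2%.

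The result assumes that 0.14 is the standardised mean paired change. The figure for 422 also assumes that every programme completer, and nobody else, has both measurements; missing paired values among completers would lower it. No rounding of the effect size brings the two-tailed requirement down to 439.

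**What to change.** Keep the two-tailed test, correct the power claim, and do not enrol more. Suggested wording: *With 439 evaluable participants, a two-tailed paired t test at alpha .05 has 83% power for a standardised mean change of 0.14, or 90% power for 0.155. With the 422 completers, power is 82% for 0.14, or 90% for 0.158, if all have paired values.* The second sentence belongs with the achieved numbers, marked as such.

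If a one-tailed test really was intended, the Sample Size paragraph must say so and the description of the analysis must be changed to match. Restating the power is preferable, because moving to a one-tailed test after data collection would weaken the analysis in order to preserve a number.

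The cost is one sentence in the article, and in the statistical analysis plan if it repeats the figure. The stated power becomes less favourable. Analysis is reported as ongoing, so the correction can be made before results appear.

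### The only power statement is for a paired t test, so it does not apply to the primary outcome, a single-arm responder proportion

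*Protocol article*

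**What the plan says.** The Aims and Objectives section states: "The primary objective is to determine the proportion of participants who achieve at least a 0.6% reduction" in HbA1c. The Primary Outcome section defines the same quantity at the end of the study. Absolute change in HbA1c is listed first under Secondary Outcomes, followed by changes in BMI, waist circumference, fasting glucose and lipids. The Study Design section describes a single arm without a comparator.

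The one sizing statement is in the Sample Size section. For a paired two-tailed t test, it says that "a sample of 439 participants will provide 90% power" "to detect a 0.14 effect size at a .05 significance level". It continues: "Considering a potential attrition rate of 12% based on the previous pilot study", "the target sample size has been set at 500 participants". The section names neither the variable behind the 0.14 nor a raw change or SD. The article gives no expected responder rate, reference rate or precision target for the primary proportion.

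The Statistical Analysis section plans descriptive summaries of all outcomes. It then names the paired t test or the Wilcoxon signed-rank test for pre-post comparison of the primary as well as the secondary measures.

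**The concern.** A power figure belongs to a particular test of a particular outcome. A paired t test concerns the mean of a within-person difference in a continuous variable. Responder status is already a summary of the change from baseline, so each participant has one value and nothing to pair it with. The sizing calculation therefore cannot be the power of the primary analysis, and the paired tests in the Statistical Analysis section cannot be applied to the primary outcome as defined.

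At stake is how the results will be read. Because the article gives only one power figure, a reader may take 90% as support for the primary finding, although no power or precision is stated for that outcome. The 0.14 is also not linked to the 0.6% threshold that defines a responder.

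**Working it through.** **Inputs from the documents.** Paired t test, two-tailed, effect size 0.14 (read as mean difference divided by the SD of differences), alpha 0.05, power 90%, 439 evaluable, 12% attrition, target 500 (Sample Size). 459 enrolled and 422 program completers (Results).

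**1. The plan's own figure.** A paired t test is a one-sample test on differences.

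- Two-sided, normal approximation: n = ((1.960 + 1.282)/0.14)² = 536.1, so 537. The noncentral t distribution gives 539.
- Power at n = 439, two-sided: 0.14 × √439 = 2.933, and Φ(2.933 − 1.960) = 83.5%. Noncentral t gives 83.3%.
- One-sided 0.05: ((1.645 + 1.282)/0.14)² = 436.9, so 437. Noncentral t gives exactly 439, with power 90.04%.
- With 439 participants and a two-sided test, 90% power needs an effect size of about 0.155.
- Attrition: 439/0.88 = 498.9, so 499, consistent with the target of 500.

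The 439 is not reproduced as labelled. It matches a one-sided calculation. At n = 422 the two-sided power is 81.8%.

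**2. What the sample gives for the primary proportion.** Half-width of the 95% interval = 1.96 × √(p(1 − p)/n). The documents give no expected rate, so a range of p is shown as an assumption.

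| p | n = 439 | n = 422 |
|---|---|---|
| 10% | 2.8 points | 2.9 points |
| 30% | 4.3 points | 4.4 points |
| 50% (worst case) | 4.7 points | 4.8 points |

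**3. Does 0.14 correspond to the 0.6% threshold?** This step assumes that the variable is HbA1c change, that 0.6% means HbA1c percentage points, that changes are normal, and that their SD lies between 0.8 and 2.0 points. None of this is stated in the Sample Size section. Mean fall = 0.14 × SD. Responder share = Φ((0.14 × SD − 0.6)/SD), compared with Φ(−0.6/SD) at zero mean change.

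| Assumed SD | Mean fall | Responders at 0.14 | Responders at zero mean change |
|---|---|---|---|
| 0.8 | 0.11 | 27.1% | 22.7% |
| 1.0 | 0.14 | 32.3% | 27.4% |
| 1.5 | 0.21 | 39.7% | 34.5% |
| 2.0 | 0.28 | 43.6% | 38.2% |

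Over this range the planning effect is a mean fall well below 0.6, and it moves the responder share by only about 4 to 5 percentage points.

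**The case against.** The best defence is that the primary objective is to determine a proportion, which is estimation without a null value. Power is then not the relevant criterion, and the sample gives reasonable precision. The Sample Size section never calls its figure the power of the primary analysis. The article is condensed, so a precision rationale may stand in the full protocol or the analysis plan.

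Most of this stands. The absence of a precision target from the article is not the fault raised here, and a reader who infers that the trial is too small for its primary outcome would go beyond the documents. What the defence does not remove is the visible mismatch. The only stated justification uses a test that cannot be applied to the primary outcome, and the Statistical Analysis section assigns that kind of test to the primary measure.

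Three further inferences are tempting but unsupported:

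- The 0.14 is not shown to be a mean HbA1c change. That is the likely reading, but any continuous paired outcome would fit the text.
- Power for the proportion against some reference rate cannot be worked out, because no reference rate is given and no such test is planned.
- The 422 are program completers. The Results section does not say that all of them have both HbA1c values.

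**Conclusion.** The point holds as a mismatch between the stated justification and the primary outcome. The 90% does not apply to the responder proportion, and the pre-post tests do not fit it. This follows from the definitions in the article and needs no assumption.

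The consequence is a wrong justification, not an inadequate sample: 439 evaluable participants estimate the proportion to within 4.7 percentage points at worst. The two-sided power of about 83% rests on reading 0.14 as a standardised paired difference. It means that relabelling the t test as secondary would not by itself make the sentence correct. The conversion of 0.14 into HbA1c points is illustrative and depends on the assumed SD.

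**What to change.** 1. **Sample Size.** Justify the primary outcome by precision, for example: *With 439 evaluable participants, the proportion with an HbA1c fall of at least 0.6% is estimated with a 95% confidence interval half-width of at most 4.7 percentage points.* If all 422 completers prove to have paired HbA1c values, at most 4.8 points may be added, labelled as achieved and not as planned.
2. **Statistical Analysis.** Report the primary proportion with its 95% confidence interval, and limit the paired t and Wilcoxon tests to the continuous secondary outcomes.
3. **The t test calculation.** State that it concerns a continuous paired outcome and name that outcome (presumably mean HbA1c change, for the authors to confirm). Replace the 90%: at 0.14, two-sided 0.05 and n = 439, power is about 83%. If a one-sided test was meant, say so and reconcile it with the two-tailed label. If 0.14 is expressed in HbA1c points, give the SD used and its source, or mark it as an assumption.

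The cost is a few sentences in two sections. Data collection has ended, and no change in sample size is needed.
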